## Abstract

**Background:**

Gastroenteropancreatic neuroendocrine carcinoma (GEP-NEC) is a group of rare but highly aggressive malignancies. The standard chemotherapy regimens composed of etoposide and cisplatin/carboplatin (EP/EC) are of limited efficacy. This prospective, multicenter, phase II study is conducted to explore the effectiveness and safety of first-line anti-PD-1 antibody (camrelizumab) combined with chemotherapy in advanced GEP-NEC patients.

**Methods:**

Patients with unresectable or metastatic GEP-NEC will receive camrelizumab combined with standard first-line chemotherapy every 3 weeks (camrelizumab 200 mg, administered intravenously on day 1; etoposide 100 mg/m^2^, administered intravenously on days 1–3; cisplatin 75 mg/m^2^, administered intravenously on day 1 or carboplatin area under the curve 5 mg/ml per min, administered intravenously on day 1). All patients were naïve to systemic therapy in the advanced setting. The primary endpoint is a 6-month progression-free survival (PFS) rate. The secondary endpoints are objective response rate, PFS, overall survival and adverse reactions.

**Discussion:**

This is the first study to investigate the therapeutic potential of camrelizumab plus chemotherapy for advanced GEP-NEC. It is expected that this trial will propose a new and effective treatment strategy for GEP-NEC in the first-line setting.

**Clinical Trial Registration:**

This trial is registered at the Chinese Clinical Trial Registry http://www.chictr.org.cn, identifier ChiCTR2100047314.

**Date of Registration:**

June 12, 2021.

## Background

According to the 2019 WHO Classification of Tumors of Digestive System, gastroenteropancreatic neuroendocrine neoplasms (GEP-NENs) are classified into well-differentiated neuroendocrine tumors (NETs), poorly differentiated neuroendocrine carcinomas (NECs), and mixed neuroendocrine–non-neuroendocrine neoplasms (1, 2). GEP-NECs are composed of highly atypical cells with high proliferative activity (>20 mitoses/2 mm^2^ or a Ki-67 index >20%) and poor prognosis. In recent decades, the incidence of GEP-NEC has been reported to have increased rapidly (3, 4).

Despite progressing understanding of NECs and emerging new therapies, the standard first-line treatment for GEP-NEC patients is still platinum-based chemotherapy, which has been used for over 30 years (5, 6). However, the efficacy and long-lasting response of platinum-based chemotherapy (etoposide and cisplatin/carboplatin, EP/EC regimens) is very limited. The reported objective response rate (ORR) ranges from 20% to 40%, with a median progression-free survival (PFS) of 2–6 months and an overall survival (OS) of 6–12 months (7). In the NORDIC NEC study, investigators retrospectively analyzed 305 patients with advanced gastrointestinal NEC and found that the ORR of the first-line platinum-based chemotherapy was 31%, with a median PFS of 4 months (95% confidence interval (CI) 3.1–4.6 months) and a median OS of 11 months (95% CI 9.4–12.6 months) (8). In fact, recommendations of the first-line platinum-based chemotherapy for GEP-NECs are mainly based on non-randomized, small sample size, and retrospective studies. Further prospective studies with new treatment approaches are in urgent need for GEP-NEC patients.

Recently, immune checkpoint inhibitors (ICIs) have shown remarkable responses in various solid malignancies, especially in tumors with a high mutational rate, deficient mismatch repair (dMMR) status, or positive PD-L1 expression. Preclinical studies have shown a high tumor mutational rate (TMB) and high frequency of positive PD-L1 expression in neuroendocrine carcinomas, which indicates immunogenic and promising responsiveness to ICIs (9–11). In small cell neuroendocrine carcinoma of the lung, which is similar to GEP-NEC in pathology, two randomized, controlled, phase 3 trials have demonstrated the survival benefits of ICIs (atezolizumab and durvalumab) combined with EP/EC chemotherapy (12, 13). Thus, atezolizumab or durvalumab combined with chemotherapy has been recommended as the standard first-line treatment for small cell lung cancer by the National Comprehensive Cancer Network (NCCN) guidelines (14). Additionally, some small size trials have revealed the efficacy and manageable toxicity of ICIs in refractory high-grade NENs (15–18). In the DART SWOG 1609 study, nivolumab plus ipilimumab showed an ORR of 44% and a 6-month PFS rate of 44% in refractory high-grade gastrointestinal and pulmonary NECs (15). A recently published study showed an encouraging response of sintilimab in refractory GEP-NECs with an ORR of 27.8% (18).

Inspired by preclinical work and immunotherapy in small cell lung cancer, we conducted this study to explore the benefit of an anti-PD-1 antibody, camrelizumab, combined with chemotherapy as first-line treatment in advanced GEP-NEC patients.

## Methods and analysis

### Study design and treatment

This prospective, multicenter, single-arm, phase II study is designed to investigate the efficacy and safety of first-line camrelizumab combined with standard chemotherapy in patients diagnosed with advanced GEP-NEC. The study protocol is formulated in accordance with the SPIRIT (Standard Protocol Items: Recommendations for Interventional Trials) statement (19). The trial has obtained ethics approval by the Chinese Ethics Committee of Registering Clinical Trials and is currently ongoing in six medical facilities in China. This protocol is version 3.0 revised on 21 January 2022.

The main inclusion criteria are pathologically confirmed locally advanced or metastatic extra-pulmonary neuroendocrine carcinoma (EP-NEC), with the primary sites located in non-pulmonary organs such as the gastrointestinal tract, pancreas, or biliary tract; without previous first-line systemic antitumor therapy since advanced GEP-NEC diagnosis; at least a 6-month interval between cancer recurrence or metastasis and the end of adjuvant chemotherapy for patients who received prior radical surgery and adjuvant chemotherapy; aged 18 to 75 years; life expectancy of over 3 months; ECOG performance status 0 or 1; at least one measurable lesion according to the Response Evaluation Criteria in Solid Tumors (RECIST) version 1.1 (20); and adequate organ function. **Table 1** lists complete inclusion and exclusion criteria.

**Table 1 T1:** Patient inclusion and exclusion criteria.

Inclusion criteria	Exclusion criteria
1. Histologically and/or cytologically confirmed, unresectable locally advanced or metastatic extrapulmonary neuroendocrine carcinoma (EP-NEC), with primary sites located in nonpulmonary organs such as the gastrointestinal tract, pancreas, or biliary tract;The pathological diagnosis of gastrointestinal neuroendocrine carcinoma will be established according to the 2019 WHO Classification of Tumours of the Digestive System; 2. Age from 18 to 75 years, either sex; 3. Life expectancy of ≥3 months; 4. Eastern Cooperative Oncology Group (ECOG) performance status score 0~1; 5. No prior first-line systemic antitumor therapy since advanced GEP-NEC diagnosis; at least a 6-month interval between cancer recurrence or metastasis and the end of adjuvant chemotherapy for patients received prior radical surgery and adjuvant chemotherapy; 6. Measurable disease according to RECIST criteria version 1.1. 7. Adequate hematologic, hepatic, and renal functions: hemoglobin ≥90 g/l, neutrophils ≥1,500/mm^3^, platelets ≥75,000/mm^3^; aspartate aminotransferase and alanine aminotransferase ≤3.0 × upper limit of normal (ULN), or ≤5.0 × ULN in case of liver metastasis; bilirubin ≤1.5 × ULN; creatinine ≤1.5 × ULN, creatinine clearance ≥50 ml/min; activated partial thromboplastin time, prothrombin time and international normalized ratio ≤1.5 × ULN; 8. In case of active hepatitis B or C, antiviral therapy starting at least 14 days before experimental drug administration and HBV DNA ≤2,500 copies/mL or ≤500IU/ml and HCV RNA within the lower limit of detection; 9. Informed consent form signed.	1. Histologically confirmed well-differentiated neuroendocrine tumor, mixed adenoneuroendocrine carcinoma, etc.; 2. Severe hepatic or renal insufficiency; 3. Myocardial infarction within 3 months; 4. Other malignancy history with disease free survival <5 years, except for curative *in situ* cervical cancer, curative skin basal cell carcinoma and curative gastrointestinal cancer by endoscopic mucoresection; 5. Current or past history of autoimmune diseases, including but not limited to: interstitial lung disease, uveitis, enteritis, nephritis, hyperthyroidism, and hypothyroidism; 6. Active pulmonary tuberculosis within 1 year; 7. Severe and uncontrolled internal medicine diseases; 8. Severe infection needing intravenous antibiotics, antifungal agents, antiviral drugs, etc.; 9. Pregnant or breastfeeding woman; man and woman unwilling to take any contraceptive measures; 10. Long-term history of chronic diarrhea, or complete intestinal obstruction; 11. Immunosuppressant or corticosteroid (systemic or local) use to suppress immune function within 2 weeks before inclusion; 12. Ever received treatment of immune checkpoint inhibitors; 13. Allergic disease history, severe hypersensitivity to experimental drugs; 14. Congenital or acquired immunodeficiency such as HIV infection; 15. Other conditions that investigators consider not suitable for this study.

Patients eligible for participation and having signed informed consents will receive camrelizumab and EP/EC chemotherapy every 3 weeks (camrelizumab 200 mg ivgtt on day 1 + etoposide 100 mg/m^2^ ivgtt on days 1–3 + cisplatin 75 mg/m^2^ ivgtt on day 1 or carboplatin area under the curve 5 mg/ml per min, ivgtt on day 1). The total dose of cisplatin can be administered in 3 days. Treatment continues until disease progression, intolerable toxicity, patient refusal, or investigator decision. Patients will receive maintenance treatment of camrelizumab (200 mg, q3w) if disease stable or remission after 6 cycles of combination therapy. The treatment duration of camrelizumab is at most 24 months. The study design is shown in **Figure 1**.

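### Entry is open to any extrapulmonary NEC, but the objective and conclusion are for GEP-NEC only, so patients with other primaries can count in the 20 that decide the result

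*Protocol article*

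**What the plan says.** **Who may enter.** Under Study design and treatment, the Protocol article gives the main entry condition as locally advanced or metastatic "extra-pulmonary neuroendocrine carcinoma (EP-NEC), with the primary sites located in non-pulmonary organs such as the gastrointestinal tract, pancreas, or biliary tract". Table 1, criterion 1, repeats it: "with primary sites located in nonpulmonary organs such as the gastrointestinal tract, pancreas, or biliary tract". The text introduces Table 1 as the complete list of criteria. None of its 15 exclusion criteria concerns the site of the primary.

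**Whom the trial is about.** The same section says the study is "designed to investigate the efficacy and safety of first-line camrelizumab combined with standard chemotherapy in patients diagnosed with advanced GEP-NEC". The Methods part of the abstract says: "Patients with unresectable or metastatic GEP-NEC will receive camrelizumab combined with standard first-line chemotherapy every 3 weeks". The abstract's discussion says: "It is expected that this trial will propose a new and effective treatment strategy for GEP-NEC in the first-line setting". The main Discussion section is also written for GEP-NEC throughout.

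**Wording in Table 1 that presumes GEP-NEC.** Criterion 5 reads "No prior first-line systemic antitumor therapy since advanced GEP-NEC diagnosis". Criterion 1 names the WHO digestive-system classification as the pathology standard, but only for gastrointestinal NEC.

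**What is counted.** Sample size and statistical analyses counts evaluable patients, with no reference to primary site. The trial continues if at least 2 of 6 reach 6 months without progression, and the regimen is promising if at least 8 of 20 do.

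**The concern.** The document uses two population labels of different width. Extrapulmonary NEC is the broader, and it is the label in the entry rule. GEP-NEC is the narrower, and it is the label in the objective and the conclusion. Because the site list is given by example, a patient whose primary lies in another non-pulmonary organ meets criterion 1 as written and then counts in both stages of the decision rule.

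This matters more here than in a randomised trial. In a single-arm study the result is a statement about the patients who were counted, with no control group drawn from the same mixture. Each of the 20 evaluable patients is 1/20 = 5 percentage points of the observed rate. If other sites have a different 6-month PFS rate, the 8-of-20 rule answers a question about a mixture whose composition is left to chance, while the conclusion is drawn for GEP-NEC.

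**Working it through.** **Step 1. Does any text close the list?**

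| Text | Restricts entry to GEP primaries? |
|---|---|
| Study design and treatment, main inclusion criteria | No: three sites given as examples |
| Table 1, criterion 1 | No: same open wording |
| Table 1, WHO clause | No: says how gastrointestinal NEC is diagnosed and does not bar other sites |
| Table 1, criterion 5 | No: limits prior therapy and presumes a GEP-NEC diagnosis without requiring one |
| Table 1, exclusions 1 to 15 | No: none concerns primary site |
| Sample size section | No: counts evaluable patients |

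The contradiction rests on this comparison and needs no arithmetic. The rest gives a sense of size.

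**Step 2. Reproduce the stated design.** Inputs from the sample size section: target rate 50%, type I error 0.05, power 80%, continue at 2 or more of 6, promising at 8 or more of 20. For a true rate p,

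P(promising) = Σ over x = 2,…,6 of P(X₁ = x) · P(X₂ ≥ 8 − x), with X₁ ~ Bin(6, p) and X₂ ~ Bin(14, p).

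At p = 0.50 this gives 0.8055, which reproduces the stated 80% power.

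The null rate is not stated. P(promising) is 0.0269 at p = 0.20, 0.0452 at 0.22 and 0.0569 at 0.23, and it stays at or below 0.05 up to about 0.224. A search for Simon's optimal design with null 0.22 (assumed), target 0.50, type I error 0.05 and power 0.80 returns exactly this rule. I therefore use 0.22 as a working null. It is back-solved and is not a figure from the document.

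**Step 3. Mix in other sites.** Let f be the share of non-GEP patients, g the GEP rate and q the non-GEP rate. The pooled rate is m = (1 − f)g + fq, and P(promising) is evaluated at m. All values of f and q are assumptions.

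GEP patients at the working null, g = 0.22, f = 0.20:

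| q | m | P(promising) |
|---|---|---|
| 0.50 | 0.8 × 0.22 + 0.2 × 0.50 = 0.276 | 0.137 |
| 0.35 | 0.8 × 0.22 + 0.2 × 0.35 = 0.246 | 0.080 |
| 0.22 | 0.22 | 0.045 |
| 0.10 | 0.8 × 0.22 + 0.2 × 0.10 = 0.196 | 0.024 |

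Over shares of 10%, 20% and 30%, P(promising) is 0.083, 0.137 and 0.207 with q = 0.50, and 0.033, 0.024 and 0.017 with q = 0.10.

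GEP patients at the target, g = 0.50, with q = 0.22:

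| f | m | Power |
|---|---|---|
| 0 | 0.500 | 0.806 |
| 0.10 | 0.472 | 0.740 |
| 0.20 | 0.444 | 0.662 |
| 0.30 | 0.416 | 0.573 |

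**Step 4. Is the pooled approximation safe?** Fixing exactly 4 non-GEP patients among the 20, placed at random across the two stages, gives 0.130 rather than 0.137 for g = 0.22 and q = 0.50. The difference is small. A single non-GEP patient with q = 0.50 moves P(promising) only from 0.045 to 0.060.

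**The case against.** The strongest reply is that this is loose drafting. The objective names GEP-NEC, criterion 5 dates prior therapy from a GEP-NEC diagnosis, the only pathology standard named is the digestive-system classification, and all three example sites are digestive. Nothing in the document shows that a patient with another primary has been or will be enrolled. This stands as evidence of intent. It does not close the list: the open wording appears twice under a separate, broader label, and six centres without central histological review (as the Discussion acknowledges) must apply the criterion as written.

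Three stronger readings are tempting, and the document does not support them.

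- **Unknown primaries are admitted.** Criterion 1 requires primary sites located in non-pulmonary organs, so a tumour with no located primary is not plainly eligible.
- **A comparison with the historical rate is broken.** The Background cites a study in which "investigators retrospectively analyzed 305 patients with advanced gastrointestinal NEC" and gives a median PFS of 4 months. The sample size section, however, states no null rate and ties neither the 50% target nor the 8-of-20 rule to that study. The back-solved 22% does not follow from it either: with exponential PFS, a 4-month median gives 0.5^(6/4) = 35% at 6 months.
- **The open list inflates false positives.** That holds only if other sites do better. If they do worse, the chance of a positive call falls, and if they do the same, nothing changes.

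A reader might also object that analysis sets are commonly left to an analysis plan that is not shown. That is fair, and their absence is not the point here. The point is that the entry criterion and the objective, both in this document, name different populations.

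**Conclusion.** The point holds as an internal contradiction about the study population. As written, a patient with a non-GEP extrapulmonary primary is eligible and counts towards 2 of 6 and 8 of 20, while the conclusion is to be drawn for GEP-NEC.

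The size of the effect cannot be determined, because the document gives neither the share of such patients nor their 6-month PFS rate. The illustrations in the working show that a share of one in five could roughly triple the chance of a false promising call, halve it, or lower power by about 14 percentage points (0.806 − 0.662 = 0.144), depending on how the other sites behave. They rest on assumed shares and rates and on a null of 22% inferred from the decision rule. If no non-GEP patient enters, or if the rates are equal, the operating characteristics are unchanged and only the wording needs repair. The stated sample size and thresholds are not in question.

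**What to change.** Reconcile the texts in one of two ways. Both are valid, and the choice belongs to the sponsor.

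1. **Restrict to GEP-NEC.** In criterion 1 and in the matching sentence under Study design and treatment, replace the open list with a closed list of gastroenteropancreatic primaries, including biliary. If patients with other primaries are already enrolled, define a GEP-only analysis by primary site alone, without reference to outcome, and report the other sites separately.
2. **Keep extrapulmonary NEC.** Restate the objective, criterion 5 and the conclusion for extrapulmonary NEC, and report the GEP subset separately.

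The cost is a small amendment or an analysis-set definition. The target of 20 evaluable patients, about 22 enrolled and both decision thresholds stay as they are. The first option makes slightly fewer patients eligible. If non-GEP patients are already enrolled, it may also leave fewer than 20 evaluable GEP patients unless they are replaced. The sample size section describes stage 1 enrolment in the past tense, so the site-based definition should be fixed and dated before outcomes are examined. In an open single-arm trial, removing patients once outcomes are known could itself bias the result.

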**Figure 1 f1:**
[figure not shown]
Outline of the study design.

### Endpoints and assessments

The primary endpoint of this trial is the 6-month PFS rate. The secondary endpoints are ORR, PFS, OS, safety, and quality of life. The disease evaluation is performed every 9 weeks by computed tomography (CT) based on RECIST version 1.1. Patients who get radiological disease progression (PD) could be permitted to continue treatment if investigators judge the clinical benefit from the continued treatment (according to physical status, clinical symptoms, and laboratory examination results). Moreover, these patients should receive imaging examination again to determine whether they get confirmed PD after 4 weeks according to immune-related RECIST (irRECIST) (21). PFS is defined as the time from trial enrollment to first confirmed PD or death. OS is defined as the time from trial enrollment to death of any cause. And ORR is defined as the percentage of patients that obtain complete response (CR) or partial response (PR).

Serum and tissue samples will be collected before treatment start for cytokines, TMB, microsatellite instability, and PD-L1 analyses. All adverse events will be monitored during the treatment period, which will be assessed according to the Common Terminology Criteria for Adverse Events (CTCAE) version 5.0. The quality of life will be evaluated at baseline and prior to every imaging evaluation, using the validated European Organization for Research and Treatment of Cancer Quality of Life Core Questionnaire 30 (EORTC QLQ-C30) (22).

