### Sample size and statistical analyses

This study aimed to achieve a 6-month PFS rate of 50%. Sample size was determined using Simon’s optimal two-stage design for the primary endpoint of 6-month PFS rate (revised in version 4.0 of the protocol with approval from the ethics committee), with a type I error of 0.05 and 80% power. In the first stage, 6 evaluable patients were enrolled; if at least 2 patients achieved a PFS of ≥ 6 months, the study would proceed to the second stage with an additional 14 patients, for a total of 20 evaluable patients. The regimen would be considered promising if at least 8 patients in total achieved a 6-month PFS or longer. Assuming an approximately 10% non-evaluable/ dropout rate, we planned to enroll about 22 patients to obtain 20 evaluable patients.

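### With CT every 9 weeks, progression arising between week 18 and month 6 but first seen at week 27 counts as 6-month PFS, which biases the counted rate upward in both decision rules

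*Protocol article*

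**What the plan says.** Under Endpoints and assessments, the protocol article states: "The primary endpoint of this trial is the 6-month PFS rate". The same section fixes the imaging interval: "The disease evaluation is performed every 9 weeks by computed tomography (CT) based on RECIST version 1.1". It defines the time-to-event variable thus: "PFS is defined as the time from trial enrollment to first confirmed PD or death". Patients treated beyond radiological progression are imaged again to "determine whether they get confirmed PD after 4 weeks according to immune-related RECIST" (irRECIST).

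Under Sample size and statistical analyses, the target is a 6-month PFS rate of 50%, in a Simon optimal two-stage design "with a type I error of 0.05 and 80% power". The stage 1 rule is: "if at least 2 patients achieved a PFS of ≥ 6 months, the study would proceed to the second stage". Fourteen more patients then bring the total to 20 evaluable, and the regimen is called promising if at least 8 reach 6 months.

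The article schedules no scan at 6 months. It gives no rule for a progression first documented just after that date.

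**The concern.** The decision rules treat 6-month PFS as a yes/no outcome per patient, so what matters is which scans can turn a patient into a failure. On the nominal schedule the last one is week 18. The next falls about six days after the 6-month mark, so progression during the eight weeks in between is normally documented too late to count against the patient. Only death, or progression found on unscheduled imaging, is dated inside that interval.

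The error runs in one direction, towards success. It enters both the stage 1 rule and the final rule, and 20 patients in a single arm leave little margin. The stated type I error of 0.05 is at stake: a regimen no better than the null could pass more often than planned.

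**Working it through.** **Inputs from the article.** CT every 9 weeks; success means PFS of at least 6 months; continue if at least 2 of 6; promising if at least 8 of 20; target 50%; type I error 0.05; power 80%.

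**Assumptions, not in the article.** A null rate p0 of 20–22%; exponential PFS; scans on the nominal dates counted from enrolment; progression dated at the scan that shows it. Let f be the share of failures between week 18 and month 6 that are dated on time, through death or unscheduled imaging.

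**1. Reproduce the design.** The chance of passing at a success rate p is

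P(p) = Σ over x = 2..6 of Bin(x; 6, p) × Pr[Bin(14, p) ≥ 8 − x].

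P(0.50) = 0.806, which matches the stated 80%. P(0.20) = 0.027, P(0.22) = 0.045 and P(0.23) = 0.057. A search for the Simon optimal design with p1 = 0.50 and p0 = 0.22 returns exactly 2/6 and 8/20. With p0 = 0.20, 0.23 or 0.25 it returns other designs. A null of 22% is thus compatible with the design but is inferred.

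**2. Scan dates.** One month is 30.4375 days.
- 6 months = 182.6 days = week 26.1
- Week 18 = 126/30.4375 = 4.14 months
- Week 27 = 189/30.4375 = 6.21 months

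Progression first seen at week 27 therefore satisfies the 6-month criterion.

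**3. Counted rate.** With S6 the true 6-month rate, the 18-week rate is S18 = S6^(18/26.09) = S6^0.690.
- S6 = 0.20 gives S18 = 0.329
- S6 = 0.22 gives S18 = 0.352
- S6 = 0.50 gives S18 = 0.620

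The rate that the rules count is S18 − f × (S18 − S6).

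**4. Effect on the decision.** Each cell shows the counted rate, then the chance of being called promising.

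| f | True 20% | True 22% | True 50% |
|---|---|---|---|
| 1 (no bias) | 20.0%, 0.027 | 22.0%, 0.045 | 50.0%, 0.806 |
| 0.75 | 23.2%, 0.060 | 25.3%, 0.091 | 53.0%, 0.862 |
| 0.50 | 26.5%, 0.113 | 28.6%, 0.160 | 56.0%, 0.905 |
| 0.25 | 29.7%, 0.188 | 31.9%, 0.249 | 59.0%, 0.937 |
| 0 | 32.9%, 0.282 | 35.2%, 0.355 | 62.0%, 0.959 |

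**5. Role of confirmation.** Confirmation can only move the date of progression later. Progression at week 18 confirmed at week 22 (5.06 months) is still a failure. If PFS is dated at confirmation and the confirming scan slips to week 27, the same patient becomes a success.

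**6. Effect of a week-27 status rule.** S27 = S6^(27/26.09) = S6^1.035.
- S6 = 0.20: S27 = 0.189, P = 0.020
- S6 = 0.22: S27 = 0.209, P = 0.034
- S6 = 0.50: S27 = 0.488, P = 0.779

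**The case against.** The strongest reply is that the size of the bias cannot be read from the article. A reader might infer that the endpoint is really 18-week PFS. The article does not support that: death is an event on its own date, and the article itself describes rapid deterioration in this disease, so some failures between week 18 and month 6 will be dated on time. The 18-week rate is a ceiling. This stands.

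A reader might also take the f = 0 result as the trial's type I error. It is the extreme of a range, and it rests on a null that the article does not state. A constant hazard is also open to doubt, because combination therapy gives way to maintenance after 6 three-week cycles, at about week 18.

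A third temptation is to use the cited historical median PFS of 4 months. Under an exponential curve it gives 35% at 6 months and 49% at 18 weeks, and the chance of passing goes from 0.36 to 0.78. But that median is an observed figure that may already contain detection delay, so the delay might be counted twice. For the same reason one cannot say that the counted rate is incomparable with every 6-month benchmark; that depends on how the benchmark patients were scanned.

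Finally, scan windows, the start of the scan clock and event-dating rules often sit in the full protocol or SAP. Their absence from an article is no fault, and they could change the picture: a week-27 scan done a week early falls on day 182, right at the cut-off. This lowers the certainty about size. It does not remove the mismatch, because the 9-week interval and the 6-month criterion are both stated, and nothing else in the article reconciles them.

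**Conclusion.** The point holds as an upward bias of uncertain size. Followed as written on the nominal dates, the plan counts progression that occurs between week 18 and month 6, but is first seen at week 27, as success in both decision rules. The counted rate lies between the true 6-month rate and the 18-week rate: 20–33% for a true 20%, 22–35% for a true 22%, and 50–62% for a true 50%.

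Given exponential PFS and an assumed null of 20–22%, even 75% timely capture takes the false-positive probability above the stated 0.05 (0.060–0.091). At 50% capture it is about two to three times that level. The direction of the bias depends on neither the assumed null nor the exponential shape; its size depends on both and on f. The documents do not support the claim that the trial simply measures 18-week PFS.

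**What to change.** For the two decision rules only, define success as alive and without progression at the scheduled week-27 CT, with a stated window. Count as failure any earlier progression or death, and any progression first documented at that scan (where confirmation is required, once it is later confirmed). Leave the time-to-event definition of PFS, a secondary endpoint, unchanged.

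This takes a short addition to the endpoint definition and no extra scans. The cost is that the landmark becomes in effect 27 weeks. At a true 6-month rate of 50%, power is about 0.78, not 0.806, which is slightly below the stated 80% and should be restated. The false-positive probability would be 0.020–0.034 for a null of 20–22%.

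The article describes stage 1 enrolment in the past tense. If those outcomes are already known, report the result under both the present and the revised definition, so that the change cannot be read as driven by the data.
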